### Pathophysiological Mechanism of Onchocerciasis-Associated Epilepsy

The pathophysiological mechanism of OAE remains unclear. In recent studies, *O volvulus* DNA was never isolated from cerebrospinal fluid (CSF) in patients with NS [15]. However, several of the patients enrolled in these studies had taken ivermectin in the past. In 1938, before the use of ivermectin, microfilariae in CSF were described by Casis Sacre [16] in Mexican patients with onchocerciasis with NS and Nakalanga-like clinical manifestations. Dead and live microfilariae were also found in 1959 by Mazotti [17] in CSF of patients with onchocerciasis treated with diethylcarbamazepine. In 1976, Duke et al [18] noted the presence of small numbers of *O volvulus* microfilariae in the CSF (<2 mf/mL) in 5 of 8 untreated heavily infected (>100 mf/mg skin) onchocerciasis patients. During diethylcarbamazine treatment, in 10 out of 11 heavily infected patients presenting with an ocular form of onchocerciasis, the numbers of *O volvulus* microfilariae in the CSF increased even up to 8 to 31 mf/mL [18]. Patients with *O volvulus* infection receiving diethylcarbamazine were reported to develop optic atrophy, probably because of a Mazotti reaction caused by dead microfilariae present in the optic nerve [19]. Perhaps this nerve could be an entry point of the microfilariae to the brain. Another explanation for the association between onchocerciasis and epilepsy could be the occurrence of an autoimmune response related to the *O volvulus* infection [20] leading to seizures.

Ivermectin acts on the chloride-dependent channels of both glutamate and γ-aminobutyric acid, interrupting neurotransmission in invertebrates. However, in humans, several mechanisms of brain protection exist, including P-glycoprotein, present on the apical face of endothelial cells of the blood-brain barrier and coded by the MDR1 gene [21]. Therefore in humans ivermectin generally does not enter the brain [21] and would not be able to kill microfilariae inside the brain. Ivermectin could, however, reduce the microfilariae load outside the brain and either reduce the risk that additional microfilariae penetrate the brain or reduce the neurotoxic immunological response caused by the microfilarae.

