### Ivermectin Treatment May Decrease Seizure Frequency in Patients With Onchocerciasis-Associated Epilepsy

In a study in Kabarole district in Uganda in 1992, 34/91 (37%) patients reported some decrease in either the frequency or severity of seizures after 1 dose of ivermectin (150 µg/kg) [24]. After being treated with ivermectin, 13/91 (14%) individuals had no seizures for 3.7 months (on average). Seizures were unchanged in 51/91 (56%), and worsened in 6/91 (7%) [24]. In a recent trial in the DRC comparing moxidectin (an anti- *O volvulus* experimental drug with a longer half-life than ivermectin) with ivermectin, 6 (80%) out of 7 *O volvulus*-infested patients with epilepsy became seizure free after treatment with moxidectin or ivermectin (the randomization code has not been broken yet). In one person, seizure frequency was significantly reduced over the 18-month follow-up period. In this person, microfilariae remained present in skin snips, although at a lower level than before the onchocerciasis treatment. In all subjects who became seizure free, the skin snips too became microfilaria free [[name], unpublished].

To assess whether ivermectin treatment may reduce the frequency of seizures and lead to seizure freedom, we intend to conduct a short proof-of-concept randomized clinical trial to compare immediate ivermectin treatment with delayed (after 4 months) ivermectin treatment in onchocerciasis-infested persons with epilepsy. The primary outcome is seizure freedom at 4 months. Reducing the burden of epilepsy will have a major impact on quality of life and socioeconomic status of families with affected members in Africa. If we are able to demonstrate an effect of ivermectin on the frequency of seizures, this would be an extra argument that onchocerciasis is causing epilepsy and that therefore we should increase our efforts to eliminate onchocerciasis.

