### Screening of Epilepsy Patients for Onchocerca volvulus Infection

After informed consent is obtained, trial candidates with epilepsy will be tested for the presence of antibodies to the parasite antigen OV16 with the SD BIOLINE Onchocerciasis IgG4 Rapid Test (Standard Diagnostics Inc). Also, a skin snip will be taken from the left and right iliac crests with a Holtz corneoscleral punch (2 mm). One sterilized punch will be used per subject. Each snip will be weighed on an analytical balance and incubated for 24 hours in isotonic saline in a well of a flat-bottomed microtiter plate. The microfilariae that emerge will be counted using an inverted microscope. The number of microfilariae in each well and the weight of the associated skin snip before incubation will be recorded. The mean of the skin microfilarial (mf) density (mf count/weight) of snip across all 4 skin snips will be calculated and recorded as mf/mg. Skin biopsies will then be stored in 90% ethanol to be tested for *O volvulus* by an in-house polymerase chain reaction method (supplemental methods).

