### Diagnosis of Onchocerca volvulus Infection

Diagnosis of onchocerciasis infection will be made when microfilariae are detected in skin snip and/or antibodies to the parasite antigen OV16 are detected.

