### Sample Size Calculation

We expect that 4 months of treatment with AEDs (phenobarbital, carbamazepine, or sodium valproate) will lead to seizure freedom in 50% of the patients (experience of [name] in Uganda). In a clinical trial performed in Rethy (Ituri) comparing the safety and parasitological efficacy of moxidectin versus ivermectin treatment in persons with *O volvulus* infection not receiving antiepileptic treatment, 6 (80%) of 7 trial participants with epilepsy were seizure free at 4 months.

Null hypothesis: The probability of seizure freedom at 4 months for immediate ivermectin treatment is equal to the probability of seizure freedom at 4 months for delayed ivermectin treatment. If we expect that seizure freedom at 4 months will be obtained in 50% of the participants with phenobarbital alone and that with additional ivermectin treatment 80% of patients will achieve seizure freedom at 4 months, about 104 subjects (52 per group) are needed to achieve the power of 90% to reject the null hypothesis at the 5% significance level. Considering that 5% of the patients will be lost to follow-up, 110 patients will be enrolled in the trial.

All comparative analyses will be based on the intention-to-treat principle: all randomized patients will be included in the analysis according to the result of the randomization.

For the primary endpoint, the null hypothesis will be tested by comparing the observed proportion of responses in arm A with the corresponding proportion in arm B at the 1-sided 5% significance level by using the Cochran-Mantel-Haenszel test for comparison of 2 independent proportions. The Cochran-Mantel-Haenszel test will be performed controlling for baseline frequency of seizures. The same test will be used for the secondary endpoint. Change versus baseline in skin micofilarial load at month 4 will be analyzed by means of a *t* test. Frequencies of seizures will be compared between participants with and without positive microfilaria skin snips at month 4.

Patients lost to follow-up will be regarded as nonresponders. Similarly, patients for whom the AED regimen had to be adapted because of an increasing number of seizures will be considered as nonresponders. AED treatment changes because of side effects or possible interactions with other drugs will not be considered as treatment failure.

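### The t test on change in microfilarial load states no log scale or baseline adjustment and may waste power, and seizures are compared by a post-treatment skin-snip grouping with no adjustment for arm stated

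*Protocol article*

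**What the plan says.** The Endpoints section lists skin microfilarial load as a secondary endpoint. Its analysis is given under Sample Size Calculation: "Change versus baseline in skin micofilarial load at month 4 will be analyzed by means of" a t test. Neither the scale nor the one- or two-sample form is stated, and no covariate is named. The screening section defines the measurement as a mean density "across all 4 skin snips will be calculated and recorded as mf/mg".

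Entry does not require microfilariae: "Diagnosis of onchocerciasis infection will be made when microfilariae are detected in skin snip and/or antibodies to the parasite antigen OV16 are detected". The selection criteria repeat this either/or rule, so a patient can be enrolled with a zero skin count.

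The sentence after the t test adds: "Frequencies of seizures will be compared between participants with and without positive microfilaria skin snips at month 4". No adjustment is mentioned and the comparison is not called exploratory. Earlier in the same section, every comparative analysis is said to follow intention to treat, by randomised arm.

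**The concern.** There are two separate difficulties.

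**Scale.** If ivermectin removes a proportion of the microfilariae, the absolute fall in mf/mg depends on the starting load. A patient who starts at 100 and halves contributes a change of 50, one who starts at 2 contributes 1, and one who starts at 0 contributes nothing. The mean change, and still more its standard deviation, then rest on the heaviest infections. At stake is the efficiency of a named secondary endpoint and the meaning of its summary.

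**Grouping.** Snip status at month 4 is observed after arm A has received ivermectin and before arm B has. The protocol itself expects treatment to clear the skin; of the earlier patients treated with moxidectin or ivermectin it says "In all subjects who became seizure free, the skin snips too became microfilaria free". Snip-negative patients will therefore come disproportionately from arm A, joined by those who were negative or lightly infected at entry. Any effect of ivermectin on seizures, by whatever route, will appear as an association between microfilariae and seizures. The protocol's Objective says that a positive trial would strengthen the argument that onchocerciasis causes epilepsy, so this comparison is liable to be read as support for the mechanism.

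**Working it through.** **Step 1. Arm size.** The plan gives no power figure for microfilarial load, so I use its own size of 52 per arm. That figure reproduces with pooled variance, two-sided 5%, 90% power and no continuity correction: n = [1.960 × √(2 × 0.65 × 0.35) + 1.282 × √(0.25 + 0.16)]² / 0.30² = 51.0, rounded up to 52. Then 104 / 0.95 = 109.5, hence 110 enrolled.

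**Step 2. Power of the t test on untransformed change.** The documents give no distribution of load, no share of zero entrants and no measurement error, so all of these are assumptions:
- baseline log-normal, geometric mean 15 mf/mg, log-SD 1 to 2;
- 20% of patients at zero throughout;
- log-scale noise of SD 0.1 to 0.6 at each visit;
- a proportional reduction in arm A and none in arm B;
- two-sample Welch t test, two-sided 5%.

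The comparator is a linear regression of log(mf/mg + 1) at month 4 on arm and baseline log(mf/mg + 1).

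| log-SD | noise | t test, 50% reduction | t test, 90% reduction |
|---|---|---|---|
| 1.0 | 0.3 | 90% | 99% |
| 1.5 | 0.3 | 60% | 85% |
| 1.5 | 0.6 | 29% | 60% |
| 2.0 | 0.6 | 16% | 38% |

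Over the whole grid the t test's power for a 50% reduction runs from about 15% (log-SD 2, noise 0.6) to over 99% (log-SD 1, noise 0.1). Log-scale ANCOVA stays at about 95% or more for the same reduction.

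A gentler model, with noise of 0.5 at follow-up only and 20% zeros, gives the t test 92%, 65% and 40% for a 50% reduction at log-SD 1.0, 1.5 and 2.0. Log-scale ANCOVA is near 100% in all three. Raising the zero share to 40% lowers the t test to 85%, 55% and 32%.

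With no effect, the t test rejects in about 2% to 5% of runs.

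**Step 3. Seizure gap produced by arm alone.** Take the protocol's planning rates, 80% seizure-free in arm A and 50% in arm B, equal arms, and no relation between snip status and seizures within an arm. Seizure freedom stands in here for seizure frequency, for which the plan gives no figures. Let a and b be the snip-negative shares at month 4 in arms A and B (assumed).

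- Seizure-free among negatives = (0.8a + 0.5b) / (a + b)
- Seizure-free among positives = [0.8(1 − a) + 0.5(1 − b)] / (2 − a − b)

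| a / b | Negatives | Positives | Gap |
|---|---|---|---|
| 70% / 40% | 0.76 / 1.10 = 69.1% | 0.54 / 0.90 = 60.0% | 9.1 points |
| 90% / 30% | 0.87 / 1.20 = 72.5% | 0.43 / 0.80 = 53.8% | 18.8 points |
| 95% / 20% | 0.86 / 1.15 = 74.8% | 0.44 / 0.85 = 51.8% | 23.0 points |

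The true within-arm association is zero in every row.

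**The case against.** **The scale is not fixed.** The protocol never says that the change is untransformed. Recording a value in mf/mg does not settle the analysis scale, and a t test on change in log load would fit the sentence. A separate analysis plan may say so, and in the simulations with follow-up noise only, a log-change t test had 99.7% power or more. This stands in part. Untransformed change is the plainer reading, but it is a reading.

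**Skew is inferred.** A reader might take it that the trial's data are known to be highly skewed and to reach beyond 100 mf/mg. The documents do not support that. The figure belongs to an older cited study of cerebrospinal fluid, where microfilariae were found "in 5 of 8 untreated heavily infected (>100 mf/mg skin) onchocerciasis patients". Nor does the protocol state that ivermectin acts proportionally; it cites a model predicting a halving at 24 hours. Right skew is likely for a density with zeros at entry, but its degree is unknown.

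**Power need not be low.** A reader might infer from a single scenario, such as 29%, that the endpoint is badly underpowered. With mild skew and little noise the t test is adequate, so only the range is defensible.

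**Validity is not at risk.** This stands in full for the t test: it does not inflate false positives, and the primary endpoint is untouched.

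**The snip comparison is modest.** It is not a listed endpoint, no test is named, and the protocol makes no explicit causal claim from it. A reader might conclude that month-4 status is fixed by arm, or that the comparison is uninterpretable. Neither follows: status is strongly influenced by arm and baseline load, and a within-arm or adjusted description would be informative. What remains is that the text asks for neither.

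**Conclusion.** The point holds in a limited form. The t test is valid but may be inefficient: its power for a halving of load is anywhere from about 15% to over 99%, depending on skew and noise that the documents do not give. ANCOVA on the log scale kept about 95% or more across the same grid. The cause for change is that a better analysis costs nothing, not that the stated one would mislead.

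The snip-status comparison is the firmer of the two points. As written it sets aside the randomised grouping that the same section promises for all comparisons, and can show a difference of 9 to 23 percentage points in seizure freedom when microfilariae play no part within arms. That range rests on the protocol's 80% and 50% rates and on assumed snip-negative shares from 70%/40% to 95%/20%.

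**What to change.** 1. Compare arms on log(mf/mg + 1) at month 4 by ANCOVA, with baseline log(mf/mg + 1) and the randomisation strata (age and seizure frequency) as covariates. Report the between-arm ratio on that scale with a 95% confidence interval, noting that the added 1 makes it only approximately a ratio of geometric means. State how patients with a zero baseline count are handled.
2. Adjust the seizure comparison by month-4 snip status for arm, baseline load and baseline seizure frequency, or stratify it by them, and label it exploratory and non-randomised. Stratifying by arm will be thin: with 70% to 95% of arm A negative, only about 0.30 × 52 = 16 down to 0.05 × 52 = 3 arm A patients would be snip-positive.

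The cost is analysis wording. The study schedule (Table 1) already includes skin snips at screening and month 4. If a separate analysis plan already sets a log scale, the first item reduces to adding the baseline covariate and strata if absent and aligning the two texts.

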## Methods

### Study Design

This is a proof-of-concept randomized treatment trial consisting of 2 treatment arms, immediate (arm A) and delayed (4 months later) ivermectin treatment (arm B). A computer-based, preplanned age and frequency of seizures stratified randomization list will be used. The trial will not be placebo-controlled as this will be costly and we do not expect this to greatly influence reporting of seizures, our primary outcome. Epilepsy patients in both arms will additionally receive antiepileptic drugs (AEDs) following local guidelines of epilepsy treatment in DRC. Study investigators collecting and analyzing data will be blinded for treatment.

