### Ivermectin Treatment Strategy

Following recommendations, 1 dose of 150 µg/kg ivermectin (Mectizan) will be administered orally, and treatment will be directly observed. Ivermectin is generally well tolerated. Common side effects of ivermectin include fever, itching, skin rash, edema, myalgia, and headache.

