### Anti-Epileptic Drug Treatment Strategy

We designed a standard epilepsy treatment protocol for both treatment arms. To summarize, we will start with phenobarbital 100 mg once a day which may be increased to 150 to 200 mg per day after 2 months if there is insufficient seizure reduction (less than 50% reduction of seizure frequency). If there are contraindications for use of phenobarbital (intellectual or behavioral disorders) or persistent side effects, carbamazepine will be prescribed (in adults initial dose 100 to 200 mg per day, maintenance dose 400 to 1400 mg; in children initial dose is 5 mg/kg per day, maintenance dose 10 to 30 mg/kg per day). In the case of side effects related to carbamazepine, we will start with sodium valproate (in adults initial dose 400 mg per day, maintenance dose 400 to 2000 mg per day; in children initial dose 15 to 20 mg/kg per day and maintenance dose 15 to 30 mg/kg per day). In the case of carbamazepine and sodium valproate, we will prescribe initial dose in all patients and will increase this to the lowest maintenance dose at 2-week visit. In case of dose-determined side effects, dose reduction is permitted. Dose may be increased at the 2-month visit if there is insufficient seizure control (less than 50% reduction in seizure frequency). Individual treatment decisions will be made by the team physician who has received specific training in epilepsy treatment and can consult with the team neurologist. Patient and family will be informed of the following regarding epilepsy treatment [29]:

Delay in onset of effect and the time course of treatmentPotential side effects and the risk of these symptoms (seek help promptly if these are distressing)Risk of abrupt discontinuation/withdrawal symptoms on missing dosesNeed for regular follow-up

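### Whether an AED change counts as nonresponse depends on the recorded reason, which could differ by arm because patients know their arm and the deciding physician is not stated to be blinded

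*Protocol article*

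**What the plan says.** The rule stands in the protocol article under Sample Size Calculation. One sentence makes some AED changes a failure: "patients for whom the AED regimen had to be adapted because of an increasing number of seizures will be considered as nonresponders". The next exempts others: "AED treatment changes because of side effects or possible interactions with other drugs will not be considered as treatment failure". No seizure-count threshold is attached to either, and nothing is said about a patient to whom both reasons apply.

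On masking, Study Design says "The trial will not be placebo-controlled as this will be costly" and also "Study investigators collecting and analyzing data will be blinded for treatment". Under Ivermectin Treatment Strategy, "1 dose of 150 µg/kg ivermectin (Mectizan) will be administered orally, and treatment will be directly observed". On who acts, Anti-Epileptic Drug Treatment Strategy says "Individual treatment decisions will be made by the team physician who has received specific training in epilepsy treatment"; that section does not say whether this physician is blinded.

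The Endpoints section defines seizure freedom by the last month of the trial only, so a patient who had more seizures earlier, and whose AED was then changed, can still be seizure-free for the primary endpoint.

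**The concern.** A rule that turns AED rescue into nonresponse is meant to stop a successful AED change from being credited to ivermectin. It does this evenly only if the same clinical course is classified in the same way in both arms. Here the classification rests on a reason, and the reason draws on what unmasked patients report and on the judgement of a physician whose masking is not stated. Blinding the analysts does not repair a label that was assigned earlier by someone who knew the arm.

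The exemption also speaks of side effects without tying them to the AED. Ivermectin has symptoms of its own ("Common side effects of ivermectin include fever, itching, skin rash, edema, myalgia, and headache"), and during the 4-month comparison only arm A receives it. In Table 1, AED and ivermectin administration share one row that begins at t=0, so early symptoms from either drug fall in the same period. A lenient use of the exempt label in one arm would change the primary outcome with no difference in seizures.

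**Working it through.** **Step 1. Which changes are open to interpretation.** Set Anti-Epileptic Drug Treatment Strategy beside Sample Size Calculation:

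| Trigger in the AED strategy | Action in the AED strategy | Status in the endpoint rule |
|---|---|---|
| Side effects | Switch of drug, or dose reduction | Exempt |
| Less than 50% seizure reduction at 2 months | Dose increase | Not stated |
| Increasing number of seizures | No separate action given | Nonresponder |
| Side effects together with more seizures | Not addressed | Depends on the reason chosen |

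The third and fourth rows show where judgement enters. The second row is a gap in the text: a patient can have less than a 50% reduction without any increase, so such a dose change is neither failure nor exempt as written. The two sections must be reconciled.

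**Step 2. Who can be misclassified.** Exemption does not make a patient a responder; month 4 must still be free of seizures. Only patients who have an AED change and are then seizure-free in month 4 can move between the categories. This uses the definition in Endpoints. The Abstract defines seizure freedom over the 4 months of follow-up; on that reading a patient with rising seizures is already a nonresponder and the label hardly matters.

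**Step 3. The plan's own figure.** For 50% against 80%, 90% power and a two-sided 5% test with pooled variance:

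n per group = [1.960 × √(2 × 0.65 × 0.35) + 1.282 × √(0.50 × 0.50 + 0.80 × 0.20)]² / 0.30² = 51.01, rounded up to 52, hence 104. Allowing for 5% loss, 104 / 0.95 = 109.5, hence 110, or 55 per arm. The stated figures reproduce and are not in dispute here.

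**Step 4. What a classification gap would do.** Let s be the share of month-4 seizure-free patients with an AED change, p the share seizure-free in month 4, and e_A and e_B the shares of those changes recorded as exempt in each arm. Then

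gap (A − B) = s × p × (e_A − e_B).

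The documents give p = 50% for AEDs alone. They give none of s, e_A and e_B, so these are assumptions:

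- e_A = e_B: gap 0, no bias.
- s = 20%, e_A = 60%, e_B = 40%: 0.20 × 0.50 × 0.20 = 2 points.
- s = 20%, e_A = 75%, e_B = 25%: 0.20 × 0.50 × 0.50 = 5 points.

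One patient in 55 is 1/55 = 1.8 points, so these gaps are about one patient (0.02 × 55 = 1.1) and about three (0.05 × 55 = 2.75).

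**Step 5. False-positive rate.** Exact binomial enumeration, 55 per arm, no ivermectin effect, unstratified pooled z test at 1-sided 5% as a stand-in for the planned Cochran-Mantel-Haenszel test:

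| Counted as responders, A vs B | Rejects |
|---|---|
| 50% vs 50% | 5.2% |
| 52% vs 50% | 7.9% |
| 52.5% vs 50% | 8.7% |
| 55% vs 50% | 13.6% |

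The normal approximation gives 7.6% and 13.1% for gaps of 2 and 5 points, so the result does not hang on the method.

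**The case against.** The strongest reply is that the AED strategy already separates the actions. Side effects lead to a switch or a dose reduction, and poor control leads to an increase, so an increase for seizures could not credibly be recorded as a side-effect change. This stands, and it confines the problem mainly to a switch or other change in a patient with both symptoms and more seizures.

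Second, the side-effect triggers in that section, and the structured questionnaire under Baseline and Follow-Up Procedures, concern the AEDs, which both arms take under one protocol. This makes it likely that AED side effects were meant. The exempting sentence does not say so, and one added phrase would settle it.

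Third, those who collect data are stated to be blinded, and a condensed article that is silent on the physician's masking does not show that the physician is unblinded. This also stands. The point is that the masking of the person who decides is not stated, while patients are unmasked in any case.

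A reader might infer that exempt reasons will arise more often in arm A, because only arm A has ivermectin symptoms and chronic medication is an exclusion criterion. The documents do not support this. They give no side-effect or interaction rates by arm, describe ivermectin as generally well tolerated, report no interaction between ivermectin and the AEDs, and do not say that ivermectin symptoms lead to AED changes. The exclusion applies at entry and does not rule out drugs started later in either arm. Nor is the direction certain: if symptoms led to less AED in arm A, more seizures there could work against ivermectin.

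**Conclusion.** The concern holds in a limited form. The primary outcome depends partly on a recorded reason, patients know their arm, and the physician who decides AED changes is not stated to be blinded, so classification could differ by arm. The documents do not show that it would, or in which direction.

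The figure of about 8 to 14%, against 5.2% with equal classification, is an illustration. It assumes no ivermectin effect, 55 per arm, 50% responders, a 1-sided 5% test and a net gap of 2 to 5 points in favour of arm A. Equal recording gives no inflation. A larger gap can be computed (60% vs 50% would reject in 28.3% of trials), but under the formula in step 4 a 10-point gap needs, for example, 20% of seizure-free patients with a change, all exempt in arm A and none in arm B. Nothing in the documents supports so extreme a split.

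Separately, and without any assumption, the endpoint status of a 2-month increase for insufficient reduction is undefined.

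**What to change.** 1. In Sample Size Calculation, state that the exempt side effects are side effects of the AED.
2. Have the investigators who are already blinded classify every AED change as failure or exempt, from diary and visit data with the arm and ivermectin records concealed, before the analysis.
3. Add a sensitivity analysis of the primary endpoint in which every AED change, for any reason, counts as nonresponse in both arms.
4. Reconcile Anti-Epileptic Drug Treatment Strategy with Sample Size Calculation, so that the endpoint status of a 2-month increase for less than 50% reduction is fixed in advance. This concerns classification only; the treatment rules are for the investigators to settle.

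A mechanical diary threshold is not a good substitute for step 2. At an unchanged 2 seizures per month, the entry minimum, the expected 2-week count is 1, and a Poisson count exceeds it with probability 1 − 2e⁻¹ = 26%. The diary is also kept by unmasked patients, so step 2 reduces the risk without removing it, and step 3 shows how far the result depends on the labels.

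The cost is a few sentences, a short blinded classification and one extra analysis. The diary and visit data are already planned. The sensitivity analysis will have somewhat fewer responders.
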